#### **3.2 Specific aims:**

- To evaluate the repercussions of isometric and isotonic exercises on pain and function in individuals with RC tendinopathy;
- To verify the effects of isometric and isotonic exercises on neuromuscular control of the shoulder complex muscles through electromyographic activity during maximal isometric contractions and on the motor task of arm arm elevation in individuals with RC tendinopathy;
- To analyze the relationship between effects on pain, neuromuscular control, functional performance and function of the shoulder complex;
- To verify the effects of isometric exercise compared to isotonic exercise on the variables described, immediately after an exercise session and after six weeks of intervention in individuals with RC tendinopathy.

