## 5.2 Sample

Forty-six individuals with a clinical diagnosis of unilateral tendinopathy of the supraspinatus and/or infraspinatus tendon by means of ultrasonography (US) or nuclear magnetic resonance (NMR) exams, between 18 and 60 years of age, of both sexes will participate in this study. They will be randomly divided and allocated into two exercise groups, with 23 individuals each: 1) isometric group, which will undergo an isometric resistance training protocol for the RC musculature associated with a stretching and strengthening protocol focused on the periscapular musculature; and 2) isotonic group, which will undergo an isotonic resistance training protocol for the RC musculature associated with a stretching and strengthening protocol focused on the periscapular musculature.

Sampling will be non-probabilistic type of consecutive cases, where individuals will be recruited from a waiting list for physiotherapeutic care in the Physical Therapy Department of UFRN and through dissemination carried out at UFRN, in the city of Natal-RN and social media through posters. The sample size was determined considering the main outcome variable, pain with arm elevation without load, considering a difference between means of 2.05 and standard deviation of 2.30 in the numerical pain rating scale (NPRS) (34). Adopting a 80% Power and  $\alpha = 0.05$ , at least 21 individuals per group will be required. Considering possible sample losses of approximately 10%, the sample should be at least 23 individuals per group.

This project will be sent to the Ethics and Research Committee of UFRN (CEP/UFRN), through the registration in Plataforma Brasil, and will only start its activities after approval. All volunteers will receive a verbal and written explanation of the objectives and methodology of the study, as well as its risks and benefits; and those who agree to participate must sign an informed consent form, in accordance with Resolution 466/12 of the National Health Council, confirming their participation in the study. The project will be submitted to the Brazilian Registry of Clinical Trials (<http://www.ensaiosclinicos.gov.br/>) before

starting to recruit individuals.

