#### 5.4.2 Assessment of electromyographic activity during maximal isometric contraction and during arm elevation

The maximum isometric contractions will be performed with a dynamometer (Nextech, DFS-X1000, Nextech Global Company Limited, Thailand), which will be fixed in an apparatus that guarantees isometric contraction, and individuals will be instructed to push against the dynamometer for arm elevation and external and internal rotations as hard as possible. For arm elevation, individuals will be sitting in a chair with back support and shoulder to 90° of elevation in the scapular plane. For shoulder external and internal rotation, individuals will be sitting, shoulder positioned at 0° abduction, flexed elbow 90°

and fist in neutral position (34). Individuals will be verbally encouraged and maintain contraction for five seconds. Each test will be performed twice, with a two -minute interval between attempts, and the average values will be used in the analysis.

For arm elevation individuals will be standing and will perform arm elevation in the scapular plane (40° of humeral abduction) using a flat vertical surface as a reference. On this same surface will 30, 60, 90 and 120 degrees of elevation will be marked for each individual. After that, individuals will perform arm elevation in each of these angles with and without load, supporting a weight of 1.5 kg for those with less than 68 kg body weight and a weight of 2.5 kg for those who with more than 68.1 kg body weight (13).

During the maximum isometric contractions and arm elevation in the different angles with and without load, the electromyographic signal of the lower trapezius, serratus anterior, middle deltoid, and infraspinatus will be collected.

For the acquisition and processing of electromyographic signals, a signal an 8 channels (EMG System do Brasil®) conditioner module (MSC 1000) with digital analog converter - A/D (CAD, 12/36-60 K) with 12 bits resolution will be used. The equipment has a common rejection ratio (RMC) greater than 80 dB, with 2,000 Hz sampling frequency and the filtrate signal between 20 and 500 Hz. As the gain programmed in the converter is 50 times and 20 times in the electrodes, the signals will be amplified 1000 times. The electromyographer will be fed by a battery and connected to a notebook that will receive the signal and store it in file. EMGLAB (EMG System from Brazil®, Brazil) software will be used for digital signal analysis.

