## 5.7 Statistical analysis

Data will be analyzed statistically in a descriptive and inferential way. Mean and standard deviation will be calculated for all demographics and dependent variables. Regarding inferential analyses, initially, the Shapiro-Wilk Normality Test will be used to classify the distribution of each variable.

In order to perform the comparison between the two groups (isometric and isotonic) and between the evaluations, for each dependent variable, we will apply two-way ANOVA with repeated measures when the data are considered parametric and Friedman when the data are non-parametric.

When necessary, post hoc Tukey or Duncan tests will be applied, respectively. All tests will be performed using the Statistical Package for Social Sciences – SPSS, version 20.0 software, and the significance level adopted will be  $\alpha \leq 0,05$ .

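### The two-way (group by evaluation) ANOVA has no term for angle or load, and the plan does not say how eight EMG readings per person become one result for the arm-elevation task

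*Combined protocol and SAP*

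**What the plan says.** Section 5.7 sets out the inferential analysis in one sentence, opening "In order to perform the comparison between the two groups (isometric and isotonic) and between the evaluations, for each dependent variable", and then names a two-way ANOVA with repeated measures, or Friedman for non-parametric data. The two factors are group and evaluation. No dependent variable is defined for EMG, and no adjustment across outcomes is stated.

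Section 5.4.2 has participants raise the arm to 30, 60, 90 and 120 degrees, both loaded and unloaded. It records "arm elevation in the different angles with and without load, the electromyographic signal of the lower trapezius, serratus anterior, middle deltoid, and infraspinatus". It also defines three activation ratios. Section 5.4 schedules three evaluations.

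Section 3.2 states the EMG aim at the level of the task: effects on neuromuscular control during maximal contractions and "on the motor task of arm arm elevation in individuals with RC tendinopathy".

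Section 5.2 sizes the trial on a different outcome: "The sample size was determined considering the main outcome variable, pain with arm elevation without load".

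**The concern.** Two factors fill a two-way model. Once group and evaluation are in it, the four angles and two loads have nowhere to go. The eight readings come from the same shoulder in the same session and are correlated, yet nothing says whether they are analysed one by one, averaged, or modelled together.

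If they are analysed one by one, each muscle or ratio gets eight p-values that may disagree, with no rule for reading them as one finding on arm elevation. A shift that runs through the whole task is then tested only cell by cell. If they are averaged, the design collects data by angle and load that the analysis cannot use to ask whether the effect differs by angle or load. If the choice waits until the data are seen, it can follow the results.

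**Working it through.** **Inputs from the documents.** Four angles and two loads (5.4.2); four muscles and three ratios (5.4.2); three evaluations (5.4); factors group and evaluation (5.7); "at least 21 individuals per group will be required", with difference 2.05, SD 2.30, 80% power and alpha 0.05 (5.2).

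**The plan's own figure.** d = 2.05 / 2.30 = 0.891. A two-sided two-sample t-test (sidedness is not stated) has 78.4% power at 20 per group and 80.5% at 21, so the stated 21 reproduces. It covers pain only; no EMG power is given.

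**Number of analyses if each cell is a dependent variable.** Cells: 4 x 2 = 8. Measures: 4 + 3 = 7. Elevation-task ANOVAs: 7 x 8 = 56. With no true effect, the expected number of significant group-by-evaluation terms at 0.05 is 56 x 0.05 = 2.8.

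**Chance of at least one false-positive cell within one measure.** If independent: 1 - 0.95^8 = 34%. For correlated cells, simulation (10,000 runs per setting, 21 per group, equal correlation rho) gives about 30%, 26%, 19% and 12% at rho = 0.3, 0.5, 0.7 and 0.9.

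**Power for an effect common to all eight cells.** The documents give no EMG effect size, SD or between-cell correlation, so these are assumptions: the same d in each cell, equal variances, equal correlation rho, 21 per group, one between-group contrast, two-sided 0.05. The mean of eight cells has variance factor (1 + 7 rho) / 8, so its standardised effect is d / sqrt((1 + 7 rho) / 8). At rho = 0.5 and d = 0.6 this is 0.6 / sqrt(0.5625) = 0.80.

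| d per cell | one cell | pooled, rho 0.5 | pooled, rho 0.7 | pooled, rho 0.9 |
|---|---|---|---|---|
| 0.5 | 35% | 56% | 45% | 38% |
| 0.6 | 48% | 72% | 60% | 51% |
| 0.7 | 60% | 84% | 73% | 64% |

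At rho = 1 the gain is nil.

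**Power for an effect that is not common.** With d = 0.891 in one cell only, that cell has about 80% power and the eight-cell mean 7% to 9%. In four of the eight cells, the mean has 62% at rho 0.3, falling to 31% at rho 0.9.

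**Does the angle term recover a local effect?** Take d = 0.6 at one angle under both loads. Each angle mean over two loads has within-person residual variance (1 - rho) / 2. The centred effect has sum of squares 0.36 x 3/4 = 0.27. Noncentrality is (21 / 2) x 0.27 / ((1 - rho) / 2) = 5.67 / (1 - rho), on 3 and 120 degrees of freedom. That gives 8.1 at rho 0.3 (power 64%), 11.3 at 0.5 (80%), 18.9 at 0.7 (96%) and 56.7 at 0.9 (near 100%), against 48% for a single cell.

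**The case against.** A reader might infer that the plan definitely runs eight separate ANOVAs per muscle and never combines the readings. The documents do not say so. Section 5.7 leaves the EMG dependent variable undefined, and averaging over cells before a two-way ANOVA also fits the text. Separate analysis is the more natural reading, because 5.4.2 says that averages are used for the two maximal contraction trials and says nothing similar for elevation. It remains an inference, so the 56 analyses and the one-cell power are conditional on it.

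A reader might also infer that most of the collected information is discarded. That does not follow either: eight readings from one person and one electrode placement are not eight independent pieces of evidence. At rho 0.9 and d = 0.6 pooling adds less than 4 points (47.5% to 51.1%). The percentages come from a single two-sample contrast, not from the interaction over three evaluations that the model would test.

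A further objection is that effects may depend on angle. The introduction itself reports altered deltoid activation early in elevation, and an average dilutes a local effect badly, as the figures above show. This stands against simple averaging. It counts much less against a model with angle and load terms, where the angle interaction recovers such an effect better than one cell does, under equal variances and equal correlation.

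That equal-variance assumption is open to question: 5.4.2 describes filtering, rectification and smoothing but no amplitude normalisation. If variance grows with angle or load, an unweighted mean leans towards those cells and the pooled formula does not apply as it stands.

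Finally, EMG is not the sized outcome, and 5.2 makes no power claim for it.

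**Conclusion.** The concern holds as a gap in 5.7. The model has no angle or load term, and no rule turns eight readings into one answer on the task. Each available reading has a cost: up to 56 unadjusted ANOVAs with no task-level test, or an average that cannot show differences by angle or load.

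The false-positive range of 12% to 34% per measure applies only if cells are tested separately without adjustment. The power gain rests on an assumed common effect and correlation: for d = 0.6 it runs from about 24 points at rho 0.5 to under 4 at rho 0.9. The case for change therefore rests mainly on having one prespecified task-level test and a proper test of angle and load, with power as a possible benefit. The plan should be changed, but the point concerns a non-primary outcome and leaves the pain comparison untouched.

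**What to change.** In 5.7, state that each muscle and each ratio from the elevation task is analysed once, in a linear mixed model or repeated-measures ANOVA with group, evaluation, angle (4 levels) and load (2 levels), the last two within subject. Then:

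- Name group-by-evaluation over the whole task as the main EMG test.
- Prespecify the group-by-evaluation-by-angle and group-by-evaluation-by-load terms, and report per-angle or per-load estimates as follow-up to them.
- If amplitude variance differs across cells, use a model that allows unequal variances, or analyse on a log scale.

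This cuts the main elevation tests from up to 56 to 7. It needs a few sentences in 5.7 and somewhat more analysis work, and no new data or visits. The downside is that an effect confined to one angle or cell is diluted in the overall term, so the interaction has to show it.

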Active surface electrodes composed of an Ag/AgCl system associated with a conductive gel, simple differential, of bipolar configuration with dimensions of 4 cm X 2.2 cm of adhesive area and 1 cm of conductive area separated by 2 cm between electrode will be used (Miotec®, Brazil). A reference electrode of monopolar configuration will also be used, composed of an Ag/AgCl system associated with a conductive gel, with a diameter of 3.8 cm of adhesive area and 1 cm of conductive area (Miotec®, USA).

The positioning of sensors for the evaluation of lower trapezius, serratus anterior, middle deltoid and infraspinatus will follow the procedure described in

Michener et al. (46). A reference electrode will be attached to the ulnar styloid process on the contralateral side (48). Before placing the electrodes, the skin of the assessed regions will be shaved and cleaned with alcohol. The electromyographic activity will be evaluated only in the muscles of the symptomatic side, and after the tests, the individuals will be questioned about their pain, using the Numerical Pain Rating Scale (0-10, with 0 being no pain and 10 being the worst possible pain). (49).

To evaluate the amplitude of the electromyographic signal of each muscle and subsequently measure the muscle activation ratio between muscle pairs, the raw data will be filtered at a bandpass frequency of 20-450 Hz, rectified and smoothed using an algorithm of root mean square (RMS) with a 50-millisecond moving window, using Matlab software.

The ratio of muscle activation between the following pairs will be evaluated: 1) infraspinatus and middle deltoid; 2) infraspinatus and lower trapezius; and 3) lower trapezius and serratus anterior. These muscle pairs were selected since individuals with RC dysfunction have increased compensatory activity of the middle portion of the deltoid (14–16) and incoordination between the lower trapezius and serratus anterior and between the upper and lower portions of the trapezius (13).

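### The non-parametric fallback in section 5.7, Friedman followed by Duncan, contains no test of isometric against isotonic exercise, so any outcome sent there loses the trial's main comparison

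*Combined protocol and SAP*

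**What the plan says.** Section 5.7 first applies a normality gate: "the Shapiro-Wilk Normality Test will be used to classify the distribution of each variable". It then names the tests meant to compare the two groups and the assessments, outcome by outcome: "we will apply two-way ANOVA with repeated measures when the data are considered parametric and Friedman when the data are non-parametric". On follow-up tests it says: "When necessary, post hoc Tukey or Duncan tests will be applied, respectively". Read in order, this gives Tukey to the ANOVA branch and Duncan to the Friedman branch. The section also plans means and SDs for every outcome.

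No other non-parametric, ordinal or mixed model is named anywhere. The abstract mentions only the two-way repeated-measures ANOVA.

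Section 4 hypothesises that isometric exercise is superior to isotonic exercise, both immediately and after six weeks. Section 5.2 sizes the trial on "the main outcome variable, pain with arm elevation without load", measured on a 0-10 numerical rating scale. Section 5.4 sets three assessments: before session 1, after session 1, and after six weeks.

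**The concern.** The trial's question is a contrast between two independent randomised groups. One of the two branches in section 5.7 names a test that has no place for a group factor, although the sentence offers it for the group comparison as well as the time comparison. Which branch applies is decided by a significance test on the collected data. An outcome that fails the gate would therefore get a p-value for change over time in everyone combined, and no p-value or confidence interval for isometric against isotonic. The gate covers each outcome separately, so this can affect the main pain score and also the secondary scores, timed tests and muscle-activity ratios.

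**Working it through.** **Inputs.** From section 5.2: difference 2.05, SD 2.30, 80% power, alpha 0.05, 21 per group raised to 23. From section 5.4: three assessments. From section 5.4.2: a 0-10 scale. The documents do not give visit means, the within-person correlation, the sidedness of alpha, or the unit to which Shapiro-Wilk applies. Those below are assumptions.

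**1. What the trial was sized for.** The standardised difference is 2.05 / 2.30 = 0.891. The normal approximation gives n = 2 × (1.960 + 0.842)² / 0.891² ≈ 19.8, so 20 per group. The exact two-sample t-test has power 0.784 at 20 and 0.805 at 21, which reproduces the plan's figure ("at least 21 individuals per group will be required"). A one-sided test would give 16. The sample size therefore belongs to a two-sided comparison of two independent groups.

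**2. What Friedman computes.** With n participants, k visits and R_j the sum of within-participant ranks at visit j,

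Q = 12 / [n k (k+1)] × Σ R_j² − 3 n (k+1).

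For n = 46 and k = 3 this is Q = (12/552) × Σ R_j² − 552, on 2 degrees of freedom. A correction for ties changes the scaling only. Group membership appears nowhere. Using the two arms as the related conditions would require matched pairs, which independent randomised groups do not provide.

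**3. Numerical check.** Friedman was run on one simulated trial of 46 participants and three visits. The p-value was 3.9 × 10⁻⁸ both before and after the group labels were reshuffled. The table gives rejection rates at 0.05 for 23 per arm, SD 2.30, correlation 0.5, and scores rounded and clipped to 0-10.

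| True situation | Friedman, all participants | Mann-Whitney, week 6 |
|---|---|---|
| Isometric 2.05 lower at every visit, no time effect | 4.6% | 82% |
| Arms differ by 2.05 at week 6, overall average flat | 3.0% | 82% |
| Identical arms, both improve 6 to 5 to 4 | 99.8% | 5.0% |
| Both improve, isometric 2.05 better at week 6 | 99.6% | 81% |

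Friedman responds to time and not to group. In the last row it would also have rejected had the arms been the same.

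**4. Duncan.** Duncan's multiple range test compares means using an ANOVA error term. It does not operate on Friedman ranks, and it is not a substitute for a group test.

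**5. How often the gate would fire.** Same score model, 23 per arm, correlation 0.5 to 0.7:

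| Reading of the gate | Assumed visit means | Chance of a switch |
|---|---|---|
| Baseline only, arms pooled | baseline mean 4 to 6 | 0.20-0.34 |
| Any of six group-by-visit cells | 6/5.5/4 | 0.53-0.54 |
| Any of six group-by-visit cells | 5/4.5/3 | 0.68-0.71 |
| Any of six group-by-visit cells | 4/3.5/2 | 0.97 |
| Any visit, arms pooled | these paths and 5/5/4 | 0.57-1.00 |

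Part of the six-cell figure is multiplicity: six independent tests on truly normal data reject at least once with probability 1 − 0.95⁶ ≈ 0.26. For a single pooled assessment of 46 people, the rate is 0.20 at mean 5, 0.33 at mean 4 or 6, 0.83 at mean 3, and above 0.99 at mean 2 or less.

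**6. What a valid rank test would deliver.** With week-6 means of 2.95 and 5.0 and SD 2.30, Mann-Whitney has power of about 0.77 at 21 per group and 0.81 at 23. The t-test on unclipped normal data has 0.805 and 0.840. These figures are for week-6 scores. The SD of change is 2.30 × √[2(1 − ρ)], which equals 2.30 at ρ = 0.5 and is larger if the correlation is lower.

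**The case against.** The strongest reply is that the branch may never be used. No expected pain means are given, and the unit of the gate is not stated. With means of 4 to 6 at a single assessment, Shapiro-Wilk rejects in only 0.11 to 0.33 of trials, depending on whether 23 or 46 values are tested. This stands as a limit on how likely the problem is. It does not change what happens once the branch is taken.

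A reader might infer that the main outcome will probably end up without a group test because post-treatment scores pile up near zero. The documents do not support that as fact: it depends on assumed means and on a reading of the gate.

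A reader might also infer that the team would run Friedman in each arm and compare which is significant. That would be invalid, but section 5.7 does not propose it. The rate at which identical arms would disagree runs from about 0% to 49% depending on the assumed improvement and correlation, so no single figure should be attached to it.

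Finally, it may be tempting to conclude that the whole analysis must be replaced. The two-way repeated-measures ANOVA does contain a group-by-time term, and nothing here shows that branch to be wrong. It is also fair to note that planned means and SDs would still let a reader see a descriptive group difference.

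**Conclusion.** The fallback in section 5.7 cannot do the job its own sentence gives it. That follows from the structure of the test and rests on no simulation assumption. For any outcome sent down that branch, the superiority hypothesis in section 4 has no valid test and no confidence interval. For the main outcome, this is the comparison on which the sample size was built.

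The chance of this for the pain outcome is conditional: about 0.2 to 0.35 if only pooled baseline scores are tested, and about 0.5 to 1.0 if any cell or visit rejection triggers the switch. Both ranges assume SD 2.30, integer scores clipped to 0-10, 23 per arm and mean paths from 6/5.5/4 to 4/3.5/2. Even at the lower end, that is too high a chance of leaving the main comparison without a test.

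**What to change.** In section 5.7, replace Friedman and Duncan with a fallback that compares the groups. One option is Mann-Whitney with a Hodges-Lehmann confidence interval on change from baseline, isometric against isotonic, immediately after session 1 and at six weeks. If the gate is kept, state what it is applied to (arm, visit, pooled values or residuals) and which result triggers the switch.

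The alternative is to drop the Shapiro-Wilk switch, keep one model with a group term for every outcome, and check its residuals.

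The cost is a rewrite of the analysis text, with no new data, visits or participants. The rank test gives up a little power when data are normal: about 0.03 in the comparison above (0.805 − 0.77 at 21 per group, 0.840 − 0.81 at 23), part of which comes from rounding and clipping the scores.

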### **4 Hypothesis**

According to the positive and superior results presented from the isometric exercise applied to patellar tendinopathy in relation to the isotonic exercise, both immediately and after the period intervention, in pain, strength and function of the quadriceps, we hypothesize that this exercise modality will be superior to the exercise isotonic in individuals with RC tendinopathy, both immediately and after 6 weeks of intervention. We hypothesize that isometric exercise can reduce pain and improve functional performance and neuromuscular control of the shoulder complex, thus resulting in better function in this population.

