#### 5.4 Evaluation procedures

All included individuals will undergo the following assessments: a) pain and general function of the shoulder complex; b) electromyographic activity of the shoulder complex musculature during maximal isometric contractions; and c) electromyographic activity of the shoulder complex muscles during arm elevation in the scapula plane.

This evaluation sequence will be carried out in three moments: 1) initial evaluation, immediately before the first intervention session; 2) immediately after the first exercise session; and 3) after six weeks of intervention. All evaluations will be carried out by an evaluator who will not know which intervention group the individuals belong to (blind evaluator), with the interventions applied by two other trained researchers.

One week before the initial assessment, individuals will be randomly allocated using the online randomization tool for randomized clinical trials, available on the website ([www.randomization.com](http://www.randomization.com)). To guarantee the confidentiality of the allocation of individuals, this will be carried out by one of those responsible for applying the intervention, who will be the only one to know which group the individuals belong to. After determining the group, individuals will be introduced to the evaluation process and equipment, and will undergo a test to determine the elastic band to be used during periscapular muscle strengthening exercises. In addition, individuals allocated to the isometric or isotonic exercise group will perform the initial load determination test for each of the exercises. The sequences of the study procedures are described in Figure 1.

[figure not shown]

**Figure 1.** Study's flowchart.

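### Section 5.7 leaves the group comparison at each post-treatment visit to a post hoc Tukey test with no stated contrast or error term, so power and false-positive rate depend on how it is applied

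*Combined protocol and SAP*

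**What the plan says.** Section 4 states that "this exercise modality will be superior to the exercise isotonic in individuals with RC tendinopathy, both immediately and after 6 weeks of intervention". These are two between-group claims, each tied to a visit. Section 5.4 provides the data: "This evaluation sequence will be carried out in three moments", namely before the first session, straight after it, and after six weeks.

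Section 5.2 sizes the trial on pain during unloaded arm elevation, using a difference of 2.05 and an SD of 2.30 on the numerical pain scale, 80% power and alpha 0.05. The result is that "at least 21 individuals per group will be required", raised to 23 for losses. No visit is named.

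Section 5.7 compares groups and evaluations with a two-way repeated-measures ANOVA when data are treated as parametric, and with Friedman otherwise. It then adds: "When necessary, post hoc Tukey or Duncan tests will be applied, respectively". The last word of that sentence ties Tukey to the ANOVA route. Nothing else on that route would locate a group difference at a particular visit.

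**The concern.** A significant interaction shows that the two time courses differ, but not at which visit. The answer to each claim in section 4 therefore falls to the post hoc step, and that step is not defined. Section 5.7 does not say which means enter the Tukey comparison or which error mean square it uses.

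The layout makes this matter. There are six cell means: two groups of different people, each measured three times. A group difference at one visit compares different people, so its standard error must contain between-person variance. The residual that a repeated-measures ANOVA uses for its within-subject tests has that variance removed. An all-pairs Tukey over six cells also pays for 15 comparisons when two are hypothesised. An analyst following section 5.7 could choose among versions with very different power and error rates after seeing the data.

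**Working it through.** **Inputs.** From section 5.2: difference 2.05, SD 2.30, 21 per group, alpha 0.05. From section 5.4: three visits. Between-visit correlations are assumptions, because the documents give none. I used common values of 0.5, 0.7 and 0.8, and four (same-day, six-week) pairs: (0.8, 0.4), (0.9, 0.3), (0.9, 0.5) and (0.9, 0.7). Data are taken as normal with equal variances and no expected baseline difference.

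**The plan's own figure.** Standard error of a group difference at one visit: 2.30 × √(2/21) = 0.710. Standardised effect: 2.05 / 0.710 = 2.89. A two-sided two-sample t test on 40 df has 80.5% power at 21 per group and 78.4% at 20, so 21 is reproduced. It is the sample size for one comparison at one time point.

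**Reading 1: Tukey on the two group means at one visit.** With two means, the studentized-range critical value divided by √2 is 2.021, the same as the t critical value on 40 df. This is the t test: 80% power, 5% error.

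**Reading 2: Tukey on the group factor.** This is the group main effect, averaged over three visits including baseline. For a common correlation ρ, the SD of a person's three-visit mean is 2.30 × √((1 + 2ρ)/3). The averaged difference is 2.05 × 2/3 = 1.37 if the effect is at both post-treatment visits, and 2.05/3 = 0.68 if at six weeks only.

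| ρ | SD of mean | Power, both visits | Power, six weeks only |
|---|---|---|---|
| 0.5 | 1.88 | 63% | 21% |
| 0.7 | 2.06 | 56% | 18% |
| 0.8 | 2.14 | 52% | 17% |

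The four unequal pairs fall within these ranges.

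**Reading 3: six cells, pooled cell variance.** The 5% studentized-range value for six means on 120 df is 4.096. Divided by √2 it is 2.896, against 2.021 for the t test. The expected statistic of 2.89 sits almost exactly on that threshold, so power is about 50%. The per-comparison error is about 0.45%.

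**Reading 4: six cells, within-subject residual.** The residual mean square has expectation SD² × (1 − r), where r is the average of the three between-visit correlations, but the true variance of the group difference uses SD² in full. The critical value on 80 df is 4.129 / √2 = 2.920. The effective threshold on the correct scale is therefore 2.920 × √(1 − r). Suppose the groups truly differ only after session 1. The approximate rate of a false six-week difference is then:

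| Same-day, six-week | r | Threshold | Two-sided tail |
|---|---|---|---|
| 0.5, 0.5 | 0.50 | 2.06 | 3.9% |
| 0.9, 0.3 | 0.50 | 2.06 | 3.9% |
| 0.8, 0.4 | 0.53 | 1.99 | 4.6% |
| 0.9, 0.5 | 0.63 | 1.77 | 7.7% |
| 0.7, 0.7 | 0.70 | 1.60 | 11.0% |
| 0.9, 0.7 | 0.77 | 1.41 | 15.9% |
| 0.8, 0.8 | 0.80 | 1.31 | 19.2% |

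Requiring a significant interaction first changes little in simulation. The first three rows give about 3-5%, (0.9, 0.5) gives 8%, the two rows with six-week correlation 0.7 give 11-17%, and 0.8 gives about 19%.

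**The proposed replacement.** Adjusting for baseline reduces the SD to 2.30 × √(1 − ρ²), where ρ is the correlation of that visit with baseline. At two-sided 0.025, the Bonferroni bound for two contrasts, this formula gives 83.8% power at ρ = 0.5 and 75.5% at ρ = 0.3. Simulation, which also pays for estimating the slope, gives about 83% and 74%. The unadjusted contrast has 71%.

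**The case against.** The strongest objection is that section 5.7 names no set of means and no error term, so nothing excludes Reading 1, which is sound and matches the test that section 5.2 sizes for. That stands. A reader might infer that every application of Tukey fails here, or that Tukey requires independent means. Neither is supported: Reading 1 is exact, and equally correlated means are acceptable, so Tukey on the visit means alone, with within-subject error and under sphericity, is a legitimate comparison between evaluations.

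Two further points also stand. First, the inflated error in Reading 4 is conditional. It needs that choice of error term, a true difference that is only immediate, and fairly high correlations. At (0.5, 0.5), (0.8, 0.4) and (0.9, 0.3) the rate is at or below about 5%. With no group difference at any visit, the rate after the interaction gate was at most 1.8% in every setting examined. Second, the 80% power in section 5.2 is attached to no named visit, so it is not a promise about six weeks in particular.

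What the objection does not remove is the gap itself. The sound version of the test is one of four that the wording allows, and section 5.7 does not select it.

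**Conclusion.** The concern holds as one of under-specification. Section 5.7 does not define the group contrast that section 4 needs at each post-treatment visit, or its error term, and it makes no use of baseline as a covariate. With the plan's inputs, six-week power is 80% under the sound reading and about 50% with six cells and pooled variance. The group-factor reading, which is not specific to a visit, has about 52-63% or 17-21% power depending on the effect pattern. With six cells and the within-subject residual, the false six-week rate after a purely immediate effect runs from about 3% to about 19%, governed by the correlations and not by alpha.

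These figures rest on assumed correlations, normality and equal variances. A reader might infer that the trial will breach its 5% level, or that 21 per group is wrong. The documents support neither: the direction of the error depends on a choice not yet stated, and the sample size reproduces. The point concerns the parametric route only.

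**What to change.** In section 5.7, for group comparisons on the parametric route, replace post hoc Tukey with two planned isometric-minus-isotonic contrasts per outcome, one after session 1 and one after six weeks. Adjust each for the baseline value already collected, test it with its own standard error at that visit, report it with a 95% CI, and apply Holm across the two. Tukey may stay for comparing visit means alone, with within-subject error and sphericity addressed.

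The cost is one paragraph of wording, with no new data or participants. Holm costs some power: at the Bonferroni bound with 21 per group, baseline-adjusted power is about 83% at correlation 0.5 and 74% at 0.3, so it can fall below 80% if baseline predicts later pain only weakly. Without the adjustment it would be 71%, so the covariate recovers part or all of the power that the multiplicity rule takes.
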